3. Clinical syndrome consistent will malaria associated with documented fever (axillary temperature  38oC) or self-reported history of fever in the last 48 hours with no other cause present
4. Commenced oral quinine ≤18 hours prior to scheduled commencement of arginine
5. An indication for hospital admission (eg relative cannot look after/supervise treatment at home **but not having any warning signs or severe malaria criteria in “exclusion criteria” below)**
6. Informed consent obtained

Exclusion criteria:

1. pregnancy or lactation
2. mixed infection with *P. falciparum* and *P. vivax*
3. Warning signs ofaltered mental state and inability to sit unaided
4. features of severe/complicated malaria2 (see “severe malaria” Study 1 above),
5. diabetes
6. systolic BP <100 mmHg
7. serious underlying disease (cardiac, hepatic, kidney)
8. initial iSTAT test showing any of the following values:
   - 1. glucose < 4 mmol/L
     2. K+ ≥ 4.2 meq/L
     3. Cl- > 106 meq/L
     4. HCO3- < 20 meq/L
9. known allergy to L-arginine
10. concurrent therapy with any of the following medications:
    - 1. spironolactone,
      2. oral nitrates,
      3. phosphodiesterase inhibitor (eg sildenafil [Viagra])
      4. alpha-blocking antihypertensive agents (eg prazosin)
      5. L-arginine

All UF subjects will be treated with quinine as per standard RSMM/Depkes protocols and will commence arginine within 18 hours of commencing quinine. Height and weight will be documented in all subjects.

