**Please see Appendix 3 for the types of physiological tests that will be done and where they will be done.**

**Study 2**

***Pilot pharmacokinetic, pharmacodynamic and safety study of exogenous arginine in uncomplicated falciparum malaria:***

*Overview:* In this pilot study in uncomplicated malaria we will generate initial safety, pharmacokinetic and pharmacodynamic data for exogenous arginine administration. We will use a dose-escalation design; all doses (3-12g) will be in the low-mid range of dosages previously used safely in humans (6-30g). *Dosing:* All doses of arginine hydrochloride will be infused intravenously over 30 mins (which is the standard infusion time). Initial dosing will be 3g (n=10), increasing to 6g (n=10), increasing to 12g (n=10) if lack of significant toxicity is demonstrated at each dosing level. Each arginine dose will be added to 100ml normal saline (the standard diluent safely used in other studies) such that total concentration is ≤10% (see CRF)

In addition to arginine, all subjects will be treated with standard antimalarial drugs (currently quinine) as per standard RSMM/Depkes practice/protocols.

*Clinical measures.* Vital signs (pulse rate, BP, temperature, respiration rate), and a standardised clinical assessment (symptom/sign list) will be serially monitored over 48 hours (see table 2). ECG will be monitored from -60 to 240 mins.

*Blood sampling*:

Two venous cannulae will be placed:

A cannula in the right forearm will be used for administration of IV arginine, and for any IV fluids required after arginine administration.

A cannula in the left forearm or antecubital fossa for sampling of venous blood, placed one hour prior to arginine adminstration.

At the time of cannula insertion we will take 7 ml heparinised baseline blood. This will be the -60 minute sample: 60ul will be used for baseline iSTAT EC8+ measurement of electrolytes, glucose, urea, and bicarbonate. The remainder will be processed as per NO Study II SOP for heparinised blood.

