Once the patient has a confirmed diagnosis of falciparum malaria, has fulfilled all the inclusion criteria, has none of the exclusion criteria and has given written informed consent to participate, he/she will be allocated the next code of the study.

Randomization will be carried out in groups of 10, and each code given a sealed opaque envelope which will contain that patients’ treatment group and which will only be opened when a patient has been allocated a code number.

*Design:*

Cannula insertion and baseline sampling will be performed as in study 2. Serial vital signs, clinical assessments, and laboratory parameters of safety will be measured as in Study 2 above. As appropriate, we will use the model generated from studies 1 and 2, and modeling of any electrolyte disturbances to optimize the sampling schedule ***which will result in a reduced total number of pharmacokinetic and pharmacodynamic blood samples required compared with study 2***. The maximum total volume of blood drawn will again be ≤25ml, but because of reduced numbers of samples will likely be less. In addition we will measure preliminary biomarkers of efficacy: fever and parasite clearance times, serial lactate levels, plasma levels of endothelial adhesion molecules, biomarkers of inflammation and effects on physiological parameters (including vascular function, gas transfer and physiological deadspace), with frequency again guided by results from studies 1 and 2. The effect on NO production will be examined by serial measures of plasma NOx/creat, and exhaled NO, and effect on oxidant stress, including serial plasma glutathione (GSH):oxidised glutathione (GSSG) ratios (by HPLC)61.

Observations will continue for 24 hours after the completion of the arginine infusion, with the final assessment at this time being identical to the final assessment in study 2.

*Outcomes:*

In the arginine-treated group there will be global improvements in both biochemical (including plasma NOx/creatinine, exhaled NO) and physiological markers (including brachial artery dilatation, hyperemic blood flow on Doppler and physiological deadspace).

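### Study 3 does not hold the allocation envelope until baseline testing is finished, so on the Study 2 timetable the brachial, DLCO and urine baselines, and any pre-infusion withdrawals, can fall after allocation

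*Combined protocol and SAP*

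**What the plan says.** **Trigger for allocation.** Under Study 3, Patient numbering and randomization, once a patient has confirmed falciparum malaria, meets every entry requirement, "has none of the exclusion criteria and has given written informed consent to participate, he/she will be allocated the next code of the study". Each code has a sealed opaque envelope "which will only be opened when a patient has been allocated a code number". No later condition, such as completed baseline tests or an infusion about to start, is attached to either step.

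**Eligibility items.** The exclusion list for Studies 2 and 3 (section Patients) includes an "initial iSTAT test showing any of the following values", covering glucose, potassium, chloride and bicarbonate. The quinine criterion reads "Commenced oral quinine ≤18 hours prior to scheduled commencement of arginine". It refers to a scheduled start, so it can be satisfied before the infusion begins.

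**Baseline procedures.** Study 3, Design, says: "Cannula insertion and baseline sampling will be performed as in study 2". In Study 2 (Blood sampling) the sampling cannula is "placed one hour prior to arginine adminstration", and of the blood then drawn: "This will be the -60 minute sample: 60ul will be used for baseline iSTAT EC8+ measurement of electrolytes, glucose, urea, and bicarbonate". Table 2, which is headed stage 2, gives the remaining pre-infusion times. For Study 3 the physiological measures are listed separately, "with frequency again guided by results from studies 1 and 2".

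**Masking.** Study 3, Treatment allocation, names a saline placebo matched for volume. The documents do not say who opens the envelope, who prepares the infusion, or whether the patient and the ultrasound and lung-function operators are masked.

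**The concern.** A baseline should be measured before anyone can know the arm. If the envelope may be opened while the brachial and DLCO tests are still to be done, an operator who knows the arm could obtain a slightly lower reading in the arginine group without meaning to. That shortfall would later appear as improvement. Brachial artery dilatation and Doppler hyperemic flow, which come from the same cuff release, are both named under Study 3, Outcomes, so the exposure reaches results the trial intends to report.

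There is a second effect. A patient who withdraws, cannot perform a test or becomes ineligible between allocation and infusion is a post-randomisation loss. Had allocation come after baseline, the same patient would simply not have been randomised. The documents give no rule for analysing patients who are allocated but not infused.

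**Working it through.** **Step 1: order of events.** No Study 3 timetable exists, so the check applies the Study 2 times.

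| Event | Time (min) | Source |
| --- | --- | --- |
| Cannula, baseline blood, baseline iSTAT | -60 | Study 2, Blood sampling; Table 2 |
| First exhaled NO; dead space | -60 | Table 2 |
| Earliest completed eligibility, hence earliest allocation | about -60 | exclusion list, Studies 2 and 3; Table 2 shows no iSTAT at the clinic sample |
| Endothelial testing | -45 | Table 2 |
| DLCO; urine | -30 | Table 2 |
| Repeat exhaled NO, amino acids/NOx, iSTAT, symptoms | 0 | Table 2 |
| Infusion | 0 to 30 | footnote to Tables 1 and 2 |

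The table sorts the baseline readings into three groups.

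- *First immediate pre-infusion reading after -60 min:* endothelial testing, DLCO and urine (three rows).
- *Repeated at 0 but already read at -60 min:* exhaled NO, amino acids/NOx, iSTAT and symptoms (four rows). Each has an earlier value.
- *Only at -60 min:* dead space. It shares the slot with the eligibility iSTAT and the order within the slot is not fixed.

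Baseline blood comes from the same draw as the eligibility iSTAT, so on this timetable it precedes any allocation that depends on that result. The gap from earliest allocation to infusion is 0 - (-60) = 60 min at most. An initial iSTAT done before -60 min would allow earlier allocation and expose more baselines.

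**Step 2: which readings could be influenced.** Urine and plasma NOx are assayed later in Darwin, and iSTAT and exhaled NO are instrument readings. Brachial ultrasound depends on the operator and DLCO on effort. The mechanism fits these two.

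**Step 3: possible size.** The plan states no test, alpha or analysis model for Study 3, so there is no figure of its own to reproduce. Input from Study 3, Sample size: about 20 per group, provisional. Assumed: two-sided 5%, SD 1 before and after infusion, correlation r = 0.5, no true effect, and a baseline shift s of 0.25 or 0.5 SD in one arm.

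*Change score.* SD of change = sqrt(2(1 - r)) = sqrt(2 × 0.5) = 1. The spurious difference is s. Noncentrality = s × sqrt(n/2) = s × sqrt(10), with 38 df and critical t = 2.024.

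- s = 0.25: noncentrality 0.791, rejection probability 12.0%.
- s = 0.5: noncentrality 1.581, rejection probability 33.8%.

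*Baseline-adjusted (ANCOVA).* The adjusted difference carries r × s. Residual SD = sqrt(1 - r²) = sqrt(0.75) = 0.866.

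- s = 0.25: 0.125/0.866 = 0.144; noncentrality 0.456; about 7.3%.
- s = 0.5: 0.25/0.866 = 0.289; noncentrality 0.913; about 14.4%.

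*Post-infusion values alone.* A shift confined to the baseline adds nothing; the rate stays at 5%.

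**Step 4: losses.** One patient lost between allocation and infusion is 1/20 = 5% of an arm. No pre-infusion loss rate is given.

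**The case against.** The best defence has five parts.

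1. *The order is inferred.* Table 2 belongs to stage 2, the frequency of Study 3 physiology is still open, and the sampling schedule goes to the Data Monitoring Committee before Study 3 starts. The envelope wording sets the earliest moment of opening, not a required one. This stands. A reader might infer that baselines in Study 3 do come after randomisation; the text only permits it.

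2. *Few baselines are exposed.* A reader counting Table 2 entries after -60 min would reach seven rows. Four of those are repeats of readings taken at -60 min, so three is the firm count. This stands too, and extending the point to all lung or exhaled NO baselines would be wrong.

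3. *The larger error rates belong to change scores.* With baseline adjustment they are much smaller, and the assumed shifts have no anchor in the documents. Accepted; the figures show scale only.

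4. *The real issue is masking.* If operators are masked, the baseline shift disappears. If they are not, post-infusion readings are exposed as well, and delaying the envelope does not help those. This is correct about post-infusion readings. But the documents do not state masking, and a volume-matched placebo does not by itself show who knows the arm. The order of baseline and allocation therefore still matters.

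5. *Losses are speculative.* Losses unrelated to the arm cost precision and do not bias the comparison. True, but if the arm is known, a withdrawal need not be unrelated to it.

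What survives is a procedural gap: the plan allows the wrong order, and nothing else in it rules that order out.

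**Conclusion.** The concern holds in a limited form. The Study 3 randomisation text does not require baseline testing to be complete before the code is allocated and the envelope opened. If the Study 2 timetable is carried over and the initial iSTAT is the -60 min test, the only immediate pre-infusion endothelial, DLCO and urine readings, the time-0 repeats and any withdrawals in a window of up to about 60 min can follow allocation. Bias from knowing the arm is plausible mainly for brachial ultrasound and DLCO, and only if operators are not masked, which the documents leave open.

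Under the assumptions in the working, the false-positive rate would rise from 5% to about 12% or 34% for change scores, and to about 7% or 14% with baseline adjustment. These are illustrations and not predictions. The documents do not support the stronger reading that all baselines are compromised or that such bias will occur. This is an inexpensive improvement worth making before Study 3 is finalised.

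**What to change.** In Study 3, Patient numbering and randomization, separate enrolment from allocation:

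- give a study number at consent;
- allocate the treatment code and open the envelope only after the last pre-infusion reading has been completed and recorded, immediately before infusion;
- analyse every patient allocated from that point in the allocated arm, whether or not the infusion is started.

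This protects the brachial and DLCO baselines whatever the masking arrangements turn out to be, and moves nearly all pre-infusion losses ahead of randomisation.

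**Cost.** About a sentence on the order of steps and one on the analysis set. The infusion starts a few minutes later while it is prepared, so the actual start should be recorded as time 0. The quinine criterion refers to the scheduled start, so the schedule should allow for preparation time. Study 3's dosing, sampling and size are still to be settled and reviewed, which makes this a convenient moment for the change.

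**Limit.** The change does not protect post-infusion readings. Those depend on masking, so the same paragraph should state who opens the envelope, who prepares the infusion and whether the operators are masked.

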***Ethical issues:***

*Potential side effects of arginine:* Patients with uncomplicated malaria have mean levels of arginine *below* normal, and combined with a dose well below the standard 30g IV dose used in other settings, we do not expect significant adverse effects to occur. Whilst we believe adverse effects to be unlikely, our protocol outlined in “study 2” above allows us to detect, and if necessary rectify them:

*Standard treatment:* Regardless of whether they receive arginine, all patients will receive prompt standard antimalarial drug treatment based on standard Depkes and RSMM protocols, currently quinine. There will be no delay in starting treatment due to participation in this study.

*Blood samples:* the maximum total of 25ml of blood taken over 21-72 hours is safe. Those with significant anemia (Hb <6 g/dL) will be excluded. Serial sampling is essential for appropriate pharmacokinetic-pharmacodynamic modeling. However serial blood sampling has the potential to cause concern to patients. In northern Australia, we have successfully used flip charts during the consent process to illustrate visually the procedure of studies like this that involve blood sampling. We will use similar flip charts to demonstrate visually the total volume of blood that will be collected. The flip chart will illustrate that the very small volumes collected during serial bleeds add up to only a relatively small and safe volume of blood. The use of these flip charts have proved to be especially useful in explaining blood volumes in patients with limited education who have limited numeracy and literacy skills.

*Cannula:* The consent process will explain how the cannula will be the same as that used clinically for medications and fluids. The information process will clarify that the cannula will ensure that the serial samplings will be painless and avoid the need for further painful needlesticks or fingerpricks. We will also explain that the blood taken from the cannula will also be used for any serial clinical tests requested by the treating RSMM doctor (eg repeat parasite counts, blood glucose, repeat hemoglobin), thus avoiding painful followup fingerpricks required for clinical purposes. Moreover, the serial iSTAT readings will be useful to the treating doctor, who will be alerted to abnormal results of clinical importance.

*Consent:* The Written Subject Information Statement will be translated into Bahasa Indonesia following any revisions recommended by the NIHRD ethics committees. If Bahasa Indonesia is a second language, the information will be translated with a bilingual RSMM staff member.

*Confidentiality:* Results will be stored electronically at RSMM and later at MSHR/NIHRD, accessible to investigators only, and password protected. Data sheets will be stored in a locked, secure location at RSMM.

*Non-invasive vascular studies:* These *forearm* (*not* above elbow) measures are not painful. The subject may experience minor discomfort during inflation of pressure cuffs during the studies. This discomfort will be transient and is no worse than having blood pressure measurement in routine clinical practice.

*Lung function studies:* The pulmonary function tests to be used in this study are non-invasive and routinely used in clinical, non-research pulmonary practice in hospitals throughout the world and have been shown to be safe and reliable, even in patients with severe lung disease. The tests do not involve radiation or other risk. They have been well tolerated in our malaria studies to date

*Why not start with studies with oral arginine?*

The known variability in bioavailability of oral arginine will make it much more difficult to model the pharmacodynamic effects of arginine. Oral arginine studies in malaria will require many more dosing levels, and many more subjects at each dosing level, and potentially a greater number of blood draws. We would thus need to enroll many more patients than we currently propose. We do not believe it is ethical to significantly increase the numbers of subjects we enroll to obtain less-interpretable data, when a smaller number of carefully studied subjects given IV arginine will give better quality information. Peer-review of our proposal before submission to the Wellcome Trust was that we would be criticized scientifically for starting with oral administration for the reasons above. The greater number of subjects and greater numbers of samplings involved will increase the invasiveness involved for subjects with uncomplicated malaria. IV therapy is safe. Excluding the confounding effect of variable bioavailability by using IV administration will mean that we obtain the maximal amount of high quality data from the minimum number of subjects, and minimum number of dosing levels and samplings. Overall this will make the study ***less invasive*** than if we use oral administration.

Moreover, we need to demonstrate **proof of principle** in malaria: that a known dose of arginine is able to increase NO production or have a clinically important measurable effect on the outcomes of interest. If we start with oral arginine studies and if absorption is poor in malaria (or transport processes altered in malaria), we may discard a potentially valuable adjunctive treatment by failing to demonstrate a significant effect. If known amounts of IV arginine do not increase blood arginine levels in malaria, cannot increase NO production or do not have a measurable effect on the outcomes of interest, then the studies should stop and oral bioavailability studies will be unnecessary.

In subjects seriously unwell with severe malaria, it is likely that IV therapy will be required for any adjunctive therapy, whether it is arginine or any other potential adjunctive therapy. IV administration is our target route for administration in severe malaria. If IV arginine is effective in severe malaria, enteral/nasogastric arginine *may then* be feasible, and appropriate to study.

*Are we using a new experimental drug?* Arginine has been administered to humans orally and intravenously for decades for diagnostic and therapeutic use, with extensive safety data. It is commonly used diagnostically in humans as a 30g intravenous dose to stimulate growth hormone release. Arginine is therefore not a new experimental drug. We are simply examining whether an established natural product/drug can be used for a ***new indication*** (ie as an adjunctive treatment for malaria combined with standard antimalarial drug).

*Why not use an animal model?* No animal model of malaria is an exact model for human disease and all have limitations. Most importantly, in none of the current animal models is NO production reduced in malaria. This is in direct contrast to what happens in humans, where NO production is reduced, and where reduced NO production and low arginine levels are associated with poor outcome. The international reviewers for this proposal agreed that it would waste time, resources and animals to test arginine in animal models of malaria, because results would not be applicable to humans.

*Funding:* Funding is from the Wellcome Trust (a non-profit UK-based medical charity) and the National Health and Medical Research Council (Australia) as part of the International Collaborative Research Grants Scheme awarded jointly to NIHRD and MSHR. *No funding has or will be received from any companies manufacturing arginine.* Arginine is prepared as an inexpensive off-patent generic commercially available drug (see generic product information attached).

## Authorship/ownership of the study: will be shared by all investigators and, as appropriate, those providing significant consultant support, as per International Committee of Medical Journal Editors 2003 criteria.

*Certificate of analysis for intraveneous arginine:* This will provided to Indonesian FDA for approval following ethical review.

| **TABLE 1**  **(stage 1)**  Time (mins) | Clinic sample  (Day 0) | 0 | 60-240 | 480-720 | Day 1 | Day 1 | Day 2  § | Day 3 §§  (severe malaria only) | 1-2 week followup |
| --- | --- | --- | --- | --- | --- | --- | --- | --- | --- |
| Time (hrs) | -5 to -1 | 0 | 1-4 | 8-12 | 18-24 | 30-36 | 42-48 | ±72 | 1-2 wks |
| Volume of blood (mL) |  | 10 |  | 2 (UM only) | 2 | 2 | 2 | 2 (SM only) | 2 |
| Vital signs (BP, PR, RR) 2nd hourly for 4 hours, then 2-4 hourly |  | X | X | X | X | X | X |  | X |
| Clinical symptoms/signs 4 hourly |  | X | X | X | X | X | X | X | X |
| iSTAT EC8+ #* or electrolytes on cryopreserved plasma** | X | X | X | X | X |  | X | X |  |
| Phosphate** |  | X | X | X | X |  | X | X |  |
| Thick/thin film* | X | X | X | X |  |  | X | X | X |
| Lactate (CG4+)* |  | X | X |  | X |  | X § | X |  |
| LFTs, CK, Creatinine** |  | X |  | X | X |  | X | X |  |
| Exhaled NO* |  | X | X | X | X | X | X | X | X |
| Gas transfer (DLCO)* |  | X | X |  | X |  | X | X | X |
| Physiological dead space* |  | X | X |  | X |  | X | X |  |
| Endothelial function testing* |  | X | X |  | X |  | X | X | X |
| Amino acids (including argine), NOx, oxidant markers** |  | X | X | X | X | X | X | X | X |
| Urine (pterins, NOx)** |  |  | X*** | X | X | X | X*** | X | X |

| **TABLE 2 (stage 2)**  Time (mins) | Clinic sample | -60 | -45 | -30 | -15 | 0 | 30 | 45 | 60 | 90 | 180 | 480 | Next AM | 1-2 weeks |
| --- | --- | --- | --- | --- | --- | --- | --- | --- | --- | --- | --- | --- | --- | --- |
| Time (hrs) | -5 to -2 | -1 | -3/4 | - ½ | - ¼ | 0 | ½ | ¾ | 1 | 1 ½ | 3 | 8 | 18-24 | 1-2 weeks |
| Volume of blood (mL) |  | 7 |  |  |  | 2 | 2 | 2 | 2 | 2 | 2 | 2 | 2 | 2 |
| Vital signs (BP, PR, RR) 10-15 minutely |  | X | X | X | X |  |  |  | X | X |  |  |  |  |
| Vital signs 5-10 minutely |  |  |  |  |  | X | X | X |  |  |  |  |  |  |
| Vital signs 30 minutely |  |  |  |  |  |  |  |  |  |  | X |  |  |  |
| Vital signs 2-4 hourly |  |  |  |  |  |  |  |  |  |  |  | X | X | X |
| Clinical symptoms/signs‡ |  | X |  |  |  | X | X | X | X | X | X | X | X | X |
| iSTAT EC8+ #* |  | X |  |  |  | X | X | X | X | X | X | X | X |  |
| Phosphate ** |  | X |  |  |  |  | X | X | X | X | X | X | X |  |
| Thick/thin film* | X | X |  |  |  |  |  |  |  |  | X | X | X | X |
| Lactate at RSMM* |  | X |  |  |  |  |  |  |  |  | X |  | X |  |
| LFTs, CK, Creatinine** |  | X |  |  |  |  |  |  |  |  |  | X | X | X |
| Exhaled NO* |  | X |  |  |  | X | X | X | X | X | X | X | X | X |
| Gas transfer (DLCO)* |  |  |  | X |  |  |  |  | X |  |  |  | X | X |
| Physiological dead space* |  | X |  |  |  |  |  |  | X |  |  |  | X |  |
| Endothelial function testing* |  |  | X |  |  |  |  | X |  |  |  |  | X | X |
| Amino acids (incl. arginine), NOx, ICAM, oxidant markers** | X | X |  |  |  | X | X | X | X | X | X | X | X | X |
| Urine (pterins, NOx)** |  |  |  | X |  |  |  |  |  |  | X*** |  | X*** | X |

